### Patient and public involvement

We conducted focus groups with GPs, specialists and allied health professionals^8^ and found that while GPs are crucial to achieving optimal care of breathless patients, the multifactorial nature of dyspnoea^2^ is a diagnostic and management challenge that limits their ability to provide the correct diagnosis or best management.^6^ Focus groups with patients confirmed their tendency not to perceive dyspnoea as a problem to raise with the GPs.^36^ Development and refinement of the protocol were an iterative process in consultation with members of the steering committees, including consumers.

The BREATHE consumer panel consists of five people diagnosed with respiratory conditions or a carer of a person with a respiratory illness. The panel meets quarterly and has reviewed the protocol and participant-facing documents, as well as participating in user acceptance testing of the participant questions in the CDSS prototype on their smartphones. The consumer panel will have ongoing input into the operational conduct of the study.

### Statistical analyses

The primary outcome is change in D-12 score, which has a minimum clinically important difference of 2.83 (out of a possible score of 36).^37^ Assuming a two-arm parallel cluster trial with a baseline measure, a total of 40 GP practices (clusters) provides 90% power to detect a mean difference in D-12 of four points at 0.05 significance level. To achieve this, each practice will be expected to recruit a minimum of nine participants who will be followed up for 12 months each. Allowing for a drop-out rate of 10%, we aim to recruit 10 participants per cluster for a total of 400 participants. A conservative SD of D-12 of 15 points and individual autocorrelation (the correlation between observations from the same individual at different times) of 0.65 is assumed. These calculations are robust to values of the intra-cluster correlation coefficient up to 0.10.

The primary analysis will compare change in D-12 scores at 12 months between the CDSS and standard care arms. The analysis will be performed using a repeated-measure linear mixed model including measurements taken at baseline, 3, 6 and 12 months. The model will include the effect of the visit, the randomised group and the interaction between randomised group and visit. A random cluster effect will be used to model within-cluster correlation, and a repeated effect will be used to model within-patient correlations.

A similar approach will be used to analyse secondary outcomes with logistic regression used in place of linear regression for binary outcomes. Controlled multiple imputations^38^ will be used to assess the robustness of the primary outcome results to different missing data assumptions. Sensitivity analyses including additional covariate adjustments will also be performed. A detailed statistical analysis plan will be developed and made publicly available before any analysis.

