### Trial design

The pragmatic implementation trial will be a cluster randomised controlled 2-arm trial (RCT) in 40 primary care sites. Each arm will comprise 20 practices, outlined below:

ARM 1: pre-screening for chronic dyspnoea and standard of care management.

ARM 2: pre-screening for chronic dyspnoea and CDSS guided management

Practices will be recruited from urban, regional and rural areas and individual GPs within each practice will consent to participate. Recruitment of patients will continue for 12 months. We will purposefully sample practices from all categories to ensure representation of each region (metropolitan, regional, rural) is equal in each arm. The randomised ‘units’ in this cluster RCT are the GP practices. The GP practices will be enrolled over time, so the randomisation list will be created by an unblinded statistician and (blinded to the study team) include a schedule within each regionality using randomly permuted blocks (a mix of size two or four) to ensure balance, and we will allocate and advise the study team as sites are activated, as GP practice allocation will be unblinded to both the study team and the GP practice.

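### The 90% power belongs to a baseline-adjusted analysis, but the primary model as written compares raw change and gives about 84-89%

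*Protocol article*

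**What the plan says.** Everything at issue is in the Statistical analyses section of the protocol article.

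The sample-size paragraph reads "Assuming a two-arm parallel cluster trial with a baseline measure, a total of 40 GP practices (clusters) provides 90% power" for a difference of 4 points. It uses an SD of 15 and adds that "individual autocorrelation (the correlation between observations from the same individual at different times) of 0.65 is assumed". Nine participants per practice are to be followed for 12 months, ten are recruited to allow for 10% drop-out, and the result is called robust to an ICC of up to 0.10. The Trial design section gives the allocation: "Each arm will comprise 20 practices".

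The next paragraph sets the primary analysis: a comparison of 12-month change in D-12 between arms, from a repeated-measures linear mixed model whose outcome visits are baseline, 3, 6 and 12 months. Its fixed effects are listed in full: "The model will include the effect of the visit, the randomised group and the interaction between randomised group and visit". One random cluster effect and a within-patient repeated effect complete it. Neither a baseline covariate nor a common baseline mean for the arms is mentioned. Additional covariate adjustment appears only under sensitivity analyses.

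**The concern.** A baseline measurement can enter a trial analysis in two ways that differ in precision. Baseline adjustment (as a covariate, or by giving the arms one common baseline mean) leaves a variance factor of 1 - r². Subtracting baseline leaves 2(1 - r), which is larger whenever r is below 1. The sample-size paragraph appears to take credit for the first, while the listed fixed effects deliver the second: with a group effect free at baseline, the 12-month group-by-visit term is the between-arm difference in raw mean change.

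At stake is whether the stated power is a property of the stated primary analysis, and whether precision that the sample size relied on is given up for no gain.

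**Working it through.** **Inputs, from the article:** difference 4; SD 15; individual autocorrelation 0.65; 20 practices per arm; m = 9 analysed per practice, so N = 360; ICC 0 to 0.10; alpha 0.05.

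**Assumptions:** a two-sided test (sidedness is not stated), and practice effects that are stable over time, as a single random cluster effect implies.

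**Formulas**
- Design effect: D = 1 + (m - 1)·ICC.
- Correlation of practice means over time: r = [m·ICC + (1 - ICC)·0.65]/D.
- Variance factor: D(1 - r²) if baseline-adjusted; 2D(1 - r) for raw change; D for the 12-month value alone.
- Variance of the arm difference: 4·SD²·factor/N = 4·225·factor/360 = 2.5·factor.

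**Step 1: find the calculation behind the 90%.**
- ICC 0: D = 1, r = 0.65, factor 1 - 0.4225 = 0.5775, variance 1.444, SE 1.202.
- ICC 0.05: D = 1.4, r = 0.7625, factor 0.586, SE 1.210.
- ICC 0.10: D = 1.8, r = 0.825, factor 0.575, SE 1.199.

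Baseline adjustment therefore gives power of 90.0%, 89.6% and 90.2% by t with 38 df (91.5%, 91.1%, 91.6% by z). Both the 90% and the robustness to the ICC are reproduced. With m = 8, power is about 88% by z, so nine is the natural choice. The 12-month value alone gives 71.6% at ICC 0, falling to 47.0% at ICC 0.10 (z), so it is not the source.

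**Step 2: the written model.**
- ICC 0: factor 2(0.35) = 0.70, variance 1.75, SE 1.323.
- ICC 0.05: factor 2·1.4·0.2375 = 0.665, SE 1.289.
- ICC 0.10: factor 2·1.8·0.175 = 0.63, SE 1.255.

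| ICC | SE, baseline-adjusted | SE, written model | Ratio | Power, written model: t(38) | z |
|---|---|---|---|---|---|
| 0 | 1.202 | 1.323 | 1.10 | 83.8% | 85.6% |
| 0.05 | 1.210 | 1.289 | 1.07 | 85.6% | 87.3% |
| 0.10 | 1.199 | 1.255 | 1.05 | 87.4% | 89.0% |

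**Step 3: check on the full four-visit model.** Generalised least squares with one random cluster effect and compound symmetry within patients returns the same SEs: 1.323, 1.289 and 1.255 with the arms free at baseline. Removing only the group effect at baseline gives 1.202, 1.210 and 1.199. With complete data the 3- and 6-month visits add nothing to the free-baseline contrast.

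**Step 4: planned drop-out.** With ten enrolled and one lost per practice, losses spread over the visits, the written model gives about 85% (ICC 0) to 88% (ICC 0.10) by t, or about 86.5% to 89.8% by z. If every loss falls after 6 months, z at ICC 0.10 reaches 90.1%. The gain is about 1 point.

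**Step 5: size needed for 90% with the written model.** From ICC 0.10 to ICC 0, it is 9.8 to 10.9 completers per practice by t(38), that is 10 to 11 (12 to 13 recruited at 10% drop-out), or 9.3 to 10.3 by z.

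**Sensitivity to the meaning of 0.65.** The article defines it as the correlation between two observations on one person. Read as the total correlation, with practice effects included, the written model gives 83.8% (t) or 85.6% (z) at every ICC. Baseline adjustment then falls from 90.0% to 87.3% by t (91.5% to 88.9% by z) as the ICC rises to 0.10. The gap between the analyses remains.

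**The case against.** Four points can be made for the plan.

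*The model is valid.* This stands. A difference in change matches the stated primary outcome, and nothing here implies bias, an inflated type I error or a wrong estimand. A reader might infer that the primary analysis is invalid or the trial seriously underpowered; the article's figures support neither.

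*The loss is small and depends on conventions.* This largely stands. The article names no reference distribution, so the z range is as admissible as the t range, and at the most favourable corner, with late drop-out, the written model reaches 90.1%. The SD is called conservative: at 14 instead of 15, the written model gives 90.0% by z or 88.4% by t at ICC 0. That shows how small the effect is, but does not make the two paragraphs agree at the stated SD.

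*Parameterisation belongs in the SAP.* This stands only in part. The article condenses, and an SAP is promised before any analysis. But it names the outcome visits and every fixed effect, and lists the group as an effect in its own right. A common baseline could have been intended, but the natural reading is a group effect free at baseline.

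*Leaving the arms free at baseline may be deliberate.* Patients consent after open-label allocation of their practice, so equal baseline means are not guaranteed. This is a fair reason not to impose a common mean. It is no reason to quote power that such an analysis does not have, and baseline covariates remain available.

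**Conclusion.** The point holds as a mismatch of modest size. The 90% is the power of a baseline-adjusted analysis; the primary model as written delivers about 84-87% by t(38) or 86-89% by z with complete data, and about 1 point more once dropouts' partial data are counted. The confidence interval is about 5% (ICC 0.10) to 10% (ICC 0) wider than the sample size assumed. This is a mis-stated power and an avoidable loss of efficiency, not a critical flaw.

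It rests on a two-sided test, complete data unless noted, and stable practice effects. If practice effects drift over time and the ICC is above 0, both analyses lose power: at a cluster autocorrelation of 0.8 and ICC 0.10, t(38) gives 76.1% with baseline adjustment and 69.8% for raw change. A reader might infer that more patients must be recruited; that does not follow, because a change of model recovers the stated power at the planned size under the article's own assumptions (practice effects stable, 0.65 taken net of them).

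**What to change.** Model D-12 at 3, 6 and 12 months as outcomes, with group, visit and group-by-visit effects, and enter baseline D-12 as covariates, each interacting with visit: the individual value and the practice mean. The practice mean is needed because, with an ICC above 0, practice means correlate more strongly over time (0.825 at ICC 0.10) than individual values do, and the power calculation uses that.

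Giving the arms a common baseline mean in the four-visit model would also restore the power. The covariate form is preferable here because it does not require the plan to assert equal baseline means after open-label allocation.

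If the written model is kept, restate its power as about 84-89%, depending on the ICC and the reference distribution, and name that distribution. Holding 90% with it would need about 10 to 11 completers per practice by t(38), or 9.3 to 10.3 by z.

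The covariate option costs a change of model specification in the SAP, a matching note against the published article, and a few fixed-effect parameters. It needs no new data, since D-12 is already collected at pre-screening.

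### As written, the primary model allows for clustering of 12-month change only if practice effects are constant over visits, a condition the protocol neither states nor justifies

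*Protocol article*

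**What the plan says.** All of this is in the protocol article, under Statistical analyses, unless noted.

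- **Primary comparison:** "The primary analysis will compare change in D-12 scores at 12 months between the CDSS and standard care arms".
- **Response:** a "repeated-measure linear mixed model including measurements taken at baseline, 3, 6 and 12 months". Baseline is therefore one of the responses, not a covariate.
- **Fixed effects:** "The model will include the effect of the visit, the randomised group and the interaction between randomised group and visit". The primary comparison is then the group-by-visit term at 12 months.
- **Correlation:** "A random cluster effect will be used to model within-cluster correlation, and a repeated effect will be used to model within-patient correlations". No practice-by-visit term, random slope or robust variance is named.
- **Power:** "a total of 40 GP practices (clusters) provides 90% power to detect a mean difference in D-12 of four points at 0.05 significance level". The design is introduced with "Assuming a two-arm parallel cluster trial with a baseline measure", and the result is said to hold for an ICC up to 0.10. No correlation of practice effects across time is given.
- **Allocation (Trial design):** "Each arm will comprise 20 practices"; practices are the randomised units.

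**The concern.** A practice intercept common to all visits adds the same constant to a patient's baseline and 12-month scores, so it disappears when one is subtracted from the other. The term meant to carry the clustering then leaves the standard error of the primary contrast unchanged. What matters for that contrast is whether practices differ in how much their patients change, and the stated model has no term for this.

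The protocol gives reasons to expect such differences. The CDSS advice is non-binding (Data collection), management stays at the GP's discretion (Arm 2 procedures), and practices span metropolitan, regional and rural areas (Trial design). If practices do differ in change, the primary p-value and confidence interval of a cluster-randomised trial would be too optimistic.

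**Working it through.** **Inputs from the protocol.** SD 15 (variance 225); individual autocorrelation τ = 0.65; k = 20 practices per arm; n = 9 evaluable patients per practice ("each practice will be expected to recruit a minimum of nine participants who will be followed up for 12 months each"); ICC ρ up to 0.10; target difference 4 points; α = 0.05, taken as two-sided.

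**Assumed.** The cluster autocorrelation π (CAC), meaning the correlation between a practice's effects at two visits, is not in the document. The range 0.65 to 1 is used.

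**1. The plan's power figure.** The baseline-adjusted formula for a parallel cluster trial is

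Var = 2·225·[1+(n−1)ρ]·(1−r²)/(n·k), with r = [nρπ+(1−ρ)τ]/[1+(n−1)ρ].

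- ρ = 0: r = 0.65, Var = 450·0.5775/180 = 1.444, SE 1.202. Power is 0.915 (normal) or 0.900 (t, 38 df).
- ρ = 0.10, π = 1: r = (0.9+0.585)/1.8 = 0.825, Var = 450·1.8·0.3194/180 = 1.437, SE 1.199. Power is 0.916 or 0.902.
- ρ = 0.10, π = 0.9: r = 0.775. Power is 0.847 or 0.83.
- ρ = 0.10, π = 0.8: r = 0.725, SE 1.461. Power is 0.782 or 0.76.

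The 90%, and its stability up to ICC 0.10, are reproduced when π is at or near 1.

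**2. Cancellation.** Generalised least squares on the four-visit model with complete data, within-practice variance 225·0.9 = 202.5 and τ = 0.65:

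| Practice-intercept variance | SE(group × 12 months) | SE(group at baseline) |
|---|---|---|
| 0 | 1.255 | 1.50 |
| 22.5 | 1.255 | 2.12 |
| 100 | 1.255 | 3.50 |
| 1000 | 1.255 | 10.11 |

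The intercept affects the baseline comparison and leaves the primary contrast untouched. With missing visits the cancellation is nearly, not exactly, complete.

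**3. True against model standard error.** For the change from baseline to 12 months:

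- between-practice variance of change: B = 450ρ(1−π)
- within-practice variance of change: W = 450(1−ρ)(1−τ)
- true SE² = (2/20)(B + W/9)
- model SE² = 2(B+W)/180, because the residual matrix absorbs B as if it were patient-level variation
- ICC of change = B/(B+W); design effect DE = 1 + 8·(ICC of change)
- type I error = 2[1−Φ(1.96/√DE)]

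Example, ρ = 0.10 and π = 0.8: B = 9, W = 141.75. True SE = √(0.1·24.75) = 1.573 and model SE = √(2·150.75/180) = 1.294. ICC of change = 9/150.75 = 0.0597, DE = 1.478, type I error 10.7%.

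| ICC | CAC | True SE | Model SE | DE | Type I error |
|---|---|---|---|---|---|
| 0.10 | 1 | 1.255 | 1.255 | 1.000 | 5.0% |
| 0.02 | 0.8 | 1.377 | 1.317 | 1.092 | 6.1% |
| 0.05 | 0.8 | 1.453 | 1.309 | 1.234 | 7.8% |
| 0.10 | 0.9 | 1.423 | 1.275 | 1.246 | 7.9% |
| 0.10 | 0.8 | 1.573 | 1.294 | 1.478 | 10.7% |
| 0.10 | 0.65 | 1.775 | 1.323 | 1.800 | 14.4% |

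Fitting the stated model by REML to simulated trials (1,500 per setting, complete data, z-test) gave 8.1%, 11.0% and 15.3% for the last three rows. A t-test on practice mean changes with 38 df gave 3.8% to 5.5%.

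**4. Uneven CDSS uptake when there is a true effect.** Let the effect vary between Arm 2 practices with SD s, with no other variation in change between practices. This adds s²/20 to the true variance and s²/180 to the model's. At ρ = 0.10 the starting variance is 1.575.

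- s = 2: ratio (1.575+0.200)/(1.575+0.022) = 1.111; 95% interval non-coverage about 6.3%.
- s = 3: ratio 2.025/1.625 = 1.246; non-coverage about 7.9%.

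**The case against.** The best defence is that the article does not spell out the structure of the random cluster effect over visits. A detailed analysis plan is promised before any analysis and could add a practice-by-visit term without contradicting the text. That the intercept is constant over time is the ordinary reading, not the protocol's wording. This stands as a limit on certainty. It does not remove the point, because the article states a clustering term and does not defer it; an analysis plan that follows the sentence as it is usually understood inherits the problem. Degrees of freedom and a convergence fallback are different: they can properly be left to the analysis plan and are not counted against the protocol.

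Three stronger readings are tempting and not supported.

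- **That the standard error is too small, without qualification.** At CAC 1 it is correct. The document gives no CAC, and at low ICC the effect is small.
- **That type I error reaches about 18%.** This needs ICC 0.10 with CAC 0.5. That CAC is below the assumed individual autocorrelation of 0.65 and implies practice mean changes with SD √(450·0.10·0.5) = 4.7 points, control practices included, which exceeds the 4-point target. It is an extreme case. ICC 0.10 is itself the protocol's upper bound, not its expected value.
- **That uneven CDSS uptake inflates type I error.** If the CDSS has no effect, uneven use of it cannot make practices differ in change. It reduces interval coverage when there is a true effect, by the smaller amounts in step 4.

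**Conclusion.** The concern holds in conditional form. On the ordinary reading, the stated clustering term gives the primary contrast no protection, whatever the size of the practice variance. The primary standard error is right only if practice effects are constant from baseline to 12 months. That is a strong condition for an intervention delivered by practices and used at the GP's discretion, and it is left unstated.

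Over ICC 0.02 to 0.10 and CAC 0.65 to 0.9, the scenarios above put type I error between about 6% and 14%; at ICC 0.10 and CAC 0.8 the standard error is about 18% too small (1.294/1.573 = 0.82). These figures rest on the protocol's SD, autocorrelation and cluster size, equal clusters, complete data and an assumed CAC. The power claim appears to rest on the same constancy: at ICC 0.10, with t on 38 df, it falls from 0.90 to about 0.83 at CAC 0.9 and 0.76 at CAC 0.8.

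This should be fixed. It falls short of a must-fix because the size depends on an unknown CAC and the model can still be completed before analysis.

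**What to change.** Add a random practice-by-visit effect to the primary model, alongside the practice effect and the within-patient repeated effect. An unstructured practice-level covariance over visits, or an equivalent practice-level analysis of change, would also serve. Use small-sample degrees of freedom based on the 40 practices; the exact method and a fallback for non-convergence can go in the analysis plan. State the CAC assumed in the power calculation, and show power over a range of CAC at ICC 0.10.

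The text change is short. The cost is a wider confidence interval if practices do differ in change (by a factor of 1.573/1.294 = 1.22 at ICC 0.10 and CAC 0.8, before the degrees-of-freedom correction), a possible convergence problem with about nine patients per practice, and a power statement that may have to fall below 90%.

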### Economic evaluation

A within-trial cost-utility analysis will be conducted from a health system perspective to assess the cost-effectiveness of BREATHE CDSS over standard of care. Cost estimates will be based on all aspects of the intervention. Intervention costs associated with CDSS use will be determined from project financial records, including costs associated with ongoing technical support and maintenance of the CDSS. Hospitalisation costs and subsequent GP visits, referrals and tests, as reported at each follow-up visit, will be costed using Australian National Diagnosis Related Group cost weights and the Medicare Benefit Schedule (MBS), respectively. We will seek consent from all participants to access their MBS and Pharmaceutical Benefits Scheme data via Services Australia (EREC approval number RMS4167). The outcomes of interest will be differences in health-related quality of life measured using the EQ-5D-5L between CDSS and standard of care groups over a 12 month period.^39^ The latter will be converted into utility scores via published Australian value sets to determine the quality adjusted life year gain at 12 months. A joint modelling approach using multilevel modelling of both costs and effectiveness will be used to estimate the incremental cost per quality-adjusted life year gained and thus determine whether CDSS provides value for money. Finally, a budget impact analysis will be conducted to assess the fiscal impact on the Australian healthcare system with the potential implementation of the CDSS system at a nationwide level. A series of scenario analyses with varying different assumptions around costs, effects and the population of interest will be undertaken.

## Ethics and dissemination

The study protocol (version 3.0 23 Aug 2024) has been approved by the University of New South Wales (UNSW) Human Research Ethics Committee (HREC) (iRECS6645) and will comply with the National Health and Medical Research Council’s ethical guidelines. Participating practices and each GP will provide written, informed consent which will be collected by TGI. All patients being screened will provide electronic informed consent (e-consent). All protocol amendments will be submitted and approved through UNSW HREC and sent to all participating GP practices. Results of the study will be disseminated through various forums, including peer-reviewed publications and presentation at national and international conferences. Authorship of publications will follow ICMJE guidelines and the BREATHE publication policy, and no professional writers will be employed nor artificial intelligence used. Following the study, participating practices will be provided with a summary of the findings of the study, together with a full copy of any publications and a plain language statement for participants, which will be made available in the practice reception area.

